### Recruitment {15}

Participants will be recruited via notices on the hospital bulletin boards and online advertisements. Two sites in Seoul will recruit 45 participants each, and one site in Daejeon will recruit 36 participants. The number of participants recruited at each site can be changed as the recruitment progresses.

### Assignment of interventions: allocation

#### Sequence generation {16a}

Participants will be randomly assigned to either high-dose GBH, low-dose GBH, or placebo group in a 1:1:1 allocation ratio. A random number table for blocked randomisation will be designed for each site. The size of the block will be concealed.

#### Concealment mechanism {16b}

Participants will be sequentially numbered based on the enrollment. Allocation will be concealed, as the random number table is generated and maintained separately.

#### Implementation {16c}

The random number table for allocation will be generated by an independent statistician. The other investigators do not have access to the random number table. As the participants are enrolled in the trial, investigators will assign them a random number sequentially. Following the enrollment, participants will receive the study drug according to the assigned random number. The study drugs are packaged identically and contain either high-dose GBH, low-dose GBH, or placebo granule according to the random number table. Thus, the randomisation will be conducted without any knowledge of the principal investigators or sub-investigators.

### Assignment of interventions: blinding

#### Who will be blinded {17a}

Trial participants and investigators will be blinded. Participants will not know which study drug (high-dose GBH, low-dose GBH, or placebo granule) they are treated with. High-dose GBH, low-dose GBH, and placebo granules will be packaged identically, including the shape, colour, scent, and taste. The principal investigators, sub-investigators, clinical research coordinator, and clinical research pharmacist will be blinded to the group assignment of each participant.

#### Procedure for unblinding if needed {17b}

In case of serious medical emergencies, the code can be revealed under exceptional circumstance to determine the participant allocation. Based on the decision of the principal investigators or sub-investigators to unmask the identity of the participant, the principal investigator will hold an investigators’ meeting. If it is determined that it is necessary to unmask, the principal investigator will request breaking the participant code in writing, and the person in charge of managing random number sequence will notify the participant’s allocation information.

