
### Who will take informed consent? {26a}

The principal investigators, who are professors in the Department of Neuropsychiatry at Korean medicine hospitals, or sub-investigators, who are fellows or residents in the hospital and delegated by the principal investigators, will explain the clinical trial and the study drug in detail and seek informed consent for participation in the clinical trial. Participants will be informed that the effect of study drug is not validated, and placebo can be administered without active ingredient. Also, the standard treatment for patients with depressive disorders will be described in the informed consent form and explained by the investigators. Participants will be intensively educated to contact the investigators whenever they suspect severe depressive symptoms. The consent will be obtained prior to the screening process.

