#### Criteria for discontinuing or modifying allocated interventions {11b}

Participants are considered for treatment cessation and elimination from the study if they meet the following criteria.Participants who do not meet inclusion and exclusion criteriaParticipants with serious adverse events (SAEs)Participants with adverse events warranting discontinuation of study drugParticipants with symptom aggravation and in need of another treatmentParticipants who withdraw consentParticipants who are lost to follow-upParticipants whose compliance with treatment is below 70%Participants who are unsuitable for continuing administration by the investigators

Additionally, procedures for assessing suicide risk of participants and discontinuing intervention in case of high suicide risk were established. During 8 weeks of treatment, the depressive symptoms of participants including suicide risk will be assessed every 2 weeks. Assessment of suicide risk will be carried out using the third item of HDRS and semi-structured interview for assessing suicide risk. High suicide risk will be determined by the researcher based on the presence of specific suicide ideation or suicide attempt. Participants with high suicide risk will be discontinued from the study immediately and transferred for appropriate management and treatment.

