### Data collection and management

#### Plans for assessment and collection of outcomes {18a}

##### Primary outcome

HDRS is a representative clinician rating scale for depression. It consists of 17 items measuring the severity of depressive symptoms, and the HDRS-17 total scores range from 0 to 52, with the higher score indicating severe symptoms [28, 29]. The Korean version of HDRS validated in 2005 will be used in this study [30]. HDRS will be evaluated by trained investigators working as fellows or residents at the Department of Neuropsychiatry in Korean medicine. To ensure the consistency of HDRS, the investigators from three sites met to conduct training and discussion sessions before the initiation of clinical trial. The HDRS assessment will be carried out according to the Structured Interview Guide for the Hamilton Depression Rating Scale (SIGH-D) [31]. HDRS will be measured every 2 weeks during the 8 weeks of administration (week 0, 2, 4, 6, 8) and follow-up assessment (week 12).

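### The only emergency code-break route described puts an investigators' meeting and a written request ahead of release, which can delay access to the allocation

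*Protocol article*

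**What the plan says.** The protocol article, Procedure for unblinding if needed {17b}, opens with the purpose: "In case of serious medical emergencies, the code can be revealed under exceptional circumstance to determine the participant allocation". It then sets out the route. A principal investigator or sub-investigator decides that a participant should be unmasked, and "the principal investigator will hold an investigators’ meeting". The next step depends on what that meeting concludes: "If it is determined that it is necessary to unmask, the principal investigator will request breaking the participant code in writing". Last, "the person in charge of managing random number sequence will notify the participant’s allocation information". The section does not say who receives that notification.

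Three other places bear on this:

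- Who will be blinded {17a}: "The principal investigators, sub-investigators, clinical research coordinator, and clinical research pharmacist will be blinded to the group assignment of each participant".
- Concealment mechanism {16b} and Implementation {16c}: the random number table is produced by an independent statistician and kept apart, and the other investigators cannot see it.
- Plans for assessment and collection of outcomes {18a}, on who rates the primary outcome: "HDRS will be evaluated by trained investigators working as fellows or residents at the Department of Neuropsychiatry in Korean medicine". The consent section {26a} describes "sub-investigators, who are fellows or residents in the hospital and delegated by the principal investigators", so raters and sub-investigators come from the same staff group.

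**The concern.** An emergency unblinding procedure exists so that a clinician facing an acute problem can learn quickly what one participant has been taking. Here deliberation and paperwork come first. A sub-investigator may judge unmasking necessary, but only the principal investigator calls the meeting and makes the request, and no deputy is named. Access therefore depends on the principal investigator, the other investigators and the code keeper all being reachable, one after another. What is at stake is mainly the safety of the individual participant.

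A smaller matter concerns blinding. Section {17a} keeps principal and sub-investigators blinded to every participant's assignment, while {17b} has an allocation released without naming the recipient. The primary outcome is a clinician rating made by fellows or residents, so it is worth stating who may and may not be told.

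**Working it through.** No figure in the protocol depends on this procedure, so the check is a reading of the text, step by step.

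**Order of steps in {17b}**

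1. An emergency arises, and a principal or sub-investigator decides to unmask.
2. The principal investigator holds a meeting of investigators.
3. If the outcome is that unmasking is needed, the principal investigator asks for the code in writing.
4. The keeper of the random sequence releases the allocation.

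Step 3 is conditional on step 2. The meeting is thus a gate before release, even though an investigator has already made a decision at step 1.

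**Is another route described?**

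- Through the investigators: no. Under {16c} they have no access to the table.
- Through the pharmacy: no. The clinical research pharmacist is blinded under {17a}.
- Through an individual code at the site, or direct contact with the code keeper: neither is mentioned. The keeper acts only on the written request.

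Within the article, the four-step sequence is therefore the only way to the code.

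**Can the sequence cause delay?** Yes. Steps 2 and 3 both precede release, and each needs people to be available. How much delay cannot be said: the section gives no time limit, quorum or format for the meeting, and does not exclude one held urgently.

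**When does the allocation become known?** Only at step 4. Nobody at the step 2 meeting holds it, so the meeting cannot disclose it. Any exposure of raters could arise only from who is told at or after step 4, and on that the section is silent.

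**How far could it touch the primary outcome?** Each break concerns one participant. Section {11b} says "Participants are considered for treatment cessation and elimination from the study if they meet the following criteria", and serious adverse events are among those criteria. A participant unmasked in such an emergency may therefore contribute few later HDRS ratings, or none.

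**The case against.** The strongest reply is that this is a journal article condensing a longer protocol (version 2.8), and that sealed codes, on-call contacts and logs are the kind of detail such an article leaves out. That is fair as far as missing detail goes. It does not answer the main point, which concerns something the article does state: the meeting and the written request come before release. A fuller document would have to change that order, not merely add to it.

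A second reply is that care need not wait for the code. Section {11b} allows treatment to be stopped for serious adverse events, and has participants at high suicide risk discontinued and transferred at once, with no unblinding step. The background section also expects low risk from the product. This stands, and it limits how often a code would be wanted. But {17b} itself provides for code-breaking in emergencies, and a procedure kept for that purpose should be able to serve it.

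A reader might also infer three stronger things that the documents do not support:

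- That the meeting spreads the allocation to HDRS raters. It precedes the break, and the section names no recipient. The overlap between raters and sub-investigators makes exposure possible, not planned.
- That one revealed code gives away others in the same site's block. Sequence generation {16a} keeps the block size concealed, and {16c} keeps the table from the investigators.
- That the sequence cannot be completed in an emergency, or that the delay is without limit. No durations are given either way.

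**Conclusion.** The point holds in a narrow form. Section {17b} states an emergency purpose and then a sequence that can delay access to the allocation, and the article describes no immediate alternative. The purpose and the sequence should be reconciled.

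The size cannot be quantified from the document. With 126 participants and 8 weeks of treatment, few such events are to be expected, but each could matter to the participant concerned. Any effect on the HDRS comparison is probably small, so this is a safety and procedural point and not a finding of bias in the primary analysis. Sample size and analysis are untouched.

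The conclusion assumes that the article reports the order of steps correctly. If the full protocol already provides a direct route, the article's text needs correcting instead.

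**What to change.** Amend {17b} in three respects:

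- In an emergency, the responsible investigator can obtain that one participant's code directly, through a sealed individual code or by direct contact with the existing code keeper.
- The investigators' meeting, the written record and an entry in a code-break log follow the break instead of preceding it.
- The allocation goes only to those treating the participant and is withheld from HDRS raters. Word this so that {17a} and {17b} agree on who remains blinded and who is the exception.

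The cost is a procedural amendment, plus either individual codes or a contact arrangement with the person who already holds the sequence. The downside is somewhat less central control before a code is broken; the log and the review afterwards make each break accountable. Design, recruitment and analysis do not change.

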### Data collection and management

#### Plans for assessment and collection of outcomes {18a}

##### Primary outcome

HDRS is a representative clinician rating scale for depression. It consists of 17 items measuring the severity of depressive symptoms, and the HDRS-17 total scores range from 0 to 52, with the higher score indicating severe symptoms [28, 29]. The Korean version of HDRS validated in 2005 will be used in this study [30]. HDRS will be evaluated by trained investigators working as fellows or residents at the Department of Neuropsychiatry in Korean medicine. To ensure the consistency of HDRS, the investigators from three sites met to conduct training and discussion sessions before the initiation of clinical trial. The HDRS assessment will be carried out according to the Structured Interview Guide for the Hamilton Depression Rating Scale (SIGH-D) [31]. HDRS will be measured every 2 weeks during the 8 weeks of administration (week 0, 2, 4, 6, 8) and follow-up assessment (week 12).

##### Secondary outcomes

The HDRS-6 subscale consists of 6 items in HDRS, including depressed mood, feelings of guilt, work and activities, psychomotor retardation, psychic anxiety, and general somatic symptoms [32]. It can be used as a unidimensional measure of depressive severity, excluding insomnia and gastrointestinal symptoms [33, 34]. BDI-II, ISI, STAI, STAXI, and EQ-5D-3L are all validated self-reporting questionnaires. BDI-II is one of the patient self-rating scales for depression. It consists of 21 items measuring the severity of depressive symptoms, ranging from 0 to 63 [35]. The Korean version of BDI-II was validated in 2011 and will be used in this study [36]. ISI will be used to measure the severity of insomnia. ISI is a self-rating scale for insomnia, consisting of 7 items, and ranges from 0 to 28 [37]. The Korean version of ISI will be used in this study [38]. STAI-YZ will be used to measure the severity of anxiety symptoms [39, 40]. STAXI will be used to measure the severity of anger symptoms [41, 42]. EQ-5D-3L will be used to measure the quality of life. A certified Korean version of EQ-5D-3L will be used in this study [43, 44]. BDI-II, ISI, STAI, STAXI, and EQ-5D-3L will be measured every 4 weeks during the 8 weeks of administration (week 0, 4, 8) and follow-up assessment (week 12).

#### Plans to promote participant retention and complete follow-up {18b}

At every visit, the date of next visit will be scheduled, and the participant will be notified the day before the date of visit. The questionnaires will be checked for missing values and the participant will be requested to answer all the items listed therein.

#### Data management {19}

Data will be collected using an electronic case report form (eCRF) in the Electronic Data Capture (EDC) system of CRScube Inc. The eCRF will be designed according to the study protocol, and the data validation specification will be completed before the trial initiation. After the e-CRF release, the system query will be evaluated regularly (bi-monthly). Medical coding of adverse events and medical history will be entered using the Medical Dictionary for Regulatory Activities (MedDRA) [45]. The database will be locked following the completion of all data entry, query resolution, and medical coding procedures.

#### Confidentiality {27}

Records of participants’ personal information will be managed in accordance with relevant regulations to maintain confidentiality. The eCRF will be recorded and classified based on the participants’ identification code, and not the participant’s name. However, the clinical research associates (CRAs) who are in charge of monitoring, along with the auditor, the Institutional Review Board (IRB), and the director of Ministry of Food and Drug Safety (MFDS), may access the medical records and other source documents to verify the reliability of data in this clinical trial. The individuals or institutions with direct access to the data related to the trial have a duty of confidentiality regarding participants’ personal information. When the results of the clinical trial are published, the records used to identify the participants will remain confidential.

#### Plans for collection, laboratory evaluation, and storage of biological specimens for genetic or molecular analysis in this trial/future use {33}

None

### Statistical methods

#### Statistical methods for primary and secondary outcomes {20a}

##### Primary outcome

The change from the baseline in HDRS-17 total score at week 8 (post-treatment) among the three groups will be compared via analysis of covariance (ANCOVA). The group will be used as the fixed factor, and baseline HDRS-17 total score and site will be used as the covariate. The effect of group on HDRS-17 total score after adjusting for baseline score and site will be calculated. Subsequent pairwise comparisons will be performed with low-dose GBH vs placebo and high-dose GBH vs placebo using Dunnett’s test. The least square mean and standard error of three groups, and the estimated mean difference (95% CI) and adjusted *p*-value compared with placebo group will be presented.

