### Objectives {7}

The current phase II randomised controlled trial explores the efficacy and safety of high-dose and low-dose GBH compared with placebo in 126 patients with MDD. The primary objective is to explore whether at least one of the two doses of GBH is effective compared with placebo in patients with MDD. At the post-treatment phase (week 8), the changes from baseline in the 17-item Hamilton Depression Rating Scale (HDRS) total score will be compared among three groups. Subsequent pairwise comparisons will be carried out between the two groups treated with low-dose GBH and placebo, and high-dose GBH and placebo. Also, based on the effect sizes of GBH compared with placebo, which will be examined in this phase II trial, the feasibility of the phase III therapeutic confirmative clinical trial will be established. The secondary objectives include analysis of the efficacy of low-dose and high-dose GBH in patients with MDD compared with placebo based on HDRS response, HDRS remission, and changes from baseline on the HDRS-6 subscale and Beck Depression Inventory-II (BDI-II) at the post-treatment (week 8). The safety of GBH compared with placebo will be assessed based on the incidence of intervention-related adverse events, measurement of vital signs, clinical and laboratory evaluations, and electrocardiograms (ECGs).

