### Trial design {8}

This study will be a randomised, double-blind, placebo-controlled, and multi-arm parallel-group trial. Participants will be allocated in a 1:1:1 ratio to one of three parallel groups: high-dose GBH, low-dose GBH, and placebo. The HDRS-17 total scores in high-dose and low-dose GBH groups will be compared with those of the placebo group.

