### Sample size {14}

Sample size was computed to detect the mean difference in change from the baseline HDRS-17 total score between placebo and low-dose GBH groups. The mean difference in scores between the two groups was assumed as four, which was reported to be the threshold points for minimal improvement in patients’ perspectives [25, 26]. Also, standard deviation was estimated to be 5.78, based on the results of a similar clinical trial of *Danzhiningshen* involving patients with depression [27]. The herbal composition of GBH and Danzhiningshen differs, but the two formulae contain *Moutan Radicis Cortex*. With a two-sided significance level of 5% and a power of 80%, 33.77 participants are required in each group of the trial. Considering the drop-out rate of 20%, 42 participants will be recruited per group, and a total of 126 will be investigated.

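### Naming step-down Dunnett for the two dose-versus-placebo tests would raise power for each dose at the same 5% family-wise error; power for the primary objective would not change

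*Protocol article*

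**What the plan says.** Objectives {7} sets the primary objective as finding whether at least one of the two doses works, and then adds: "Subsequent pairwise comparisons will be carried out between the two groups treated with low-dose GBH and placebo, and high-dose GBH and placebo". The primary-outcome analysis under {20a} names the test: "Subsequent pairwise comparisons will be performed with low-dose GBH vs placebo and high-dose GBH vs placebo using Dunnett’s test". It promises an estimated difference with a 95% CI and an adjusted p-value for each dose. It does not say whether the test is single-step or step-down, or whether the intervals are simultaneous. The continuous secondary outcomes follow the same method.

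Sample size {14} rests on one pair: "Sample size was computed to detect the mean difference in change from the baseline HDRS-17 total score between placebo and low-dose GBH groups". It continues: "With a two-sided significance level of 5% and a power of 80%, 33.77 participants are required in each group of the trial". No high-dose effect is given anywhere. The Discussion adds that the trial should help to determine the dose for phase III.

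**The concern.** An unqualified Dunnett test, reported with intervals and adjusted p-values, is normally the single-step procedure. It holds both doses to one enlarged critical value. With two comparisons that is more than error control requires. By closed testing, once one dose has passed the Dunnett value, the only null hypothesis still open is that of the other dose, which may then be tested at plain two-sided 5%. The single-step test therefore gives up some power on the second dose.

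At stake is the result for each dose separately. That result bears on the dose question carried into phase III, and on the low-dose comparison, which was sized without a multiplicity adjustment.

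**Working it through.** **Inputs**
- Difference, low dose versus placebo: "The mean difference in scores between the two groups was assumed as four" (Sample size {14}).
- SD: "standard deviation was estimated to be 5.78" (same section).
- Allocation: "Participants will be allocated in a 1:1:1 ratio to one of three parallel groups" (Trial design {8}). With equal arms and a shared placebo group the two contrasts have correlation 0.5.
- Assumption: the high-dose effect. I take 4 points as the base case and show a range.

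**The plan's own figure**
- The normal approximation gives n = 2 × (5.78 × (1.960 + 0.842) / 4)² = 32.8 per group. The exact noncentral-t solution is 33.77, as stated. Power at 34 per group is 80.3% for that pair alone at unadjusted 5%.
- Dropout: 33.77 / 0.8 = 42.2, against the plan's 42. In reverse, 42 × 0.8 = 33.6, so about 34 evaluable per arm is a fair basis.

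**Critical values**
- Three arms of 34 give 102 − 3 = 99 error df. Three further df for baseline score and site leave 96.
- Two-sided Dunnett value for two contrasts: 2.244 (df 99) or 2.245 (df 96).
- Ordinary two-sided 5% t value: 1.984 (df 99) or 1.985 (df 96).

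**Rules compared**
- Single-step: declare a dose if its |t| exceeds the Dunnett value.
- Step-down: the larger |t| must exceed the Dunnett value; if it does, the other dose is tested against the ordinary t value.

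The standard error of a difference is 5.78 × √(2/34) = 1.402, so a 4-point effect has noncentrality 4 / 1.402 = 2.85.

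**Results** (1,000,000 simulated trials per scenario, 34 per arm, SD 5.78, df 99)

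| True effect, low / high | Low-dose power, single-step → step-down | Both doses, single-step → step-down |
|---|---|---|
| 4 / 4 | 72.9% → 77.6% | 59.5% → 69.0% |
| 4 / 5 | 72.8% → 79.6% | 69.3% → 77.7% |
| 4 / 6 | 72.8% → 80.5% | 72.3% → 80.2% |
| 4 / 8 | 72.8% → 80.6% | 72.8% → 80.6% |
| 3 / 4 | 46.2% → 53.8% | 40.4% → 50.4% |
| 2 / 4 | 21.2% → 28.1% | 19.6% → 27.2% |

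Power for at least one dose at 4 / 4 is 86.3% under both rules. It cannot differ, because the first step is identical.

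**Sensitivity at 4 / 4, both doses**
- With df 96: 59.4% → 68.9%.
- With all 42 per arm evaluable: 72.1% → 80.0%.
- With a significant overall F-test required first: 59.5% → 68.9%.
- With residual SD lowered by the covariates (assumed values, df 96): 76% → 83% at SD 5.0; 85% → 90% at SD 4.6.

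**Error control**
- Neither dose works: chance of any false declaration 5.0% under both rules.
- One dose gains 4 points and the other is inert: the inert dose is declared 2.7% of the time under single-step and 4.2% under step-down.

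**The case against.** The case against has several parts, and most of it limits the point without removing it.

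- **The planned test is valid.** This stands. Nothing in the article is wrong or contradictory here, and a reader should not infer that family-wise error is uncontrolled.
- **The primary objective gains nothing.** This stands. A reader might take 59% to 69% as the trial's chance of success, but Objectives {7} asks for at least one effective dose, and power for that is unchanged. Nor do two significant results choose between two doses; estimates and intervals serve that better. To speak of confirming doses would also be too strong in an exploratory phase II trial.
- **Every added rejection conflicts with its simultaneous interval.** By construction the gain comes only from trials in which the second |t| lies between about 1.985 and 2.245, where the Dunnett interval includes 0. Matching p-values and intervals is a fair reason to prefer single-step. The article, however, says only 95% CI and does not call it simultaneous. An ordinary 95% interval would agree with the second-step test. The conflict is a small reporting cost.
- **An inert dose is declared more often**, 4.2% against 2.7%. True, and still below 5%.
- **The size rests on assumptions.** The high-dose effect is not stated, and baseline adjustment may shrink the gain. Both are shown as ranges above.
- **Single-step is an inference.** It is the usual reading, but the full protocol or SAP may specify otherwise. In that case the wording only needs to be made explicit.

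**Conclusion.** The point holds as an inexpensive efficiency improvement. At the same 5% family-wise error, the single-step reading is uniformly less powerful for the second dose than step-down Dunnett.

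With 34 evaluable per arm and SD 5.78, low-dose power rises from 73% to 78% if both doses gain 4 points. If the high dose gains 6, it rises to about 80%, close to the power planned for that comparison. Power for both doses rises by about 8 to 10 points over the range of effects tried, and by about 5 to 7 points if adjustment brings the residual SD down to 4.6–5.0. The conclusion depends on the single-step reading and on an assumed high-dose effect. The documents do not support a claim that the planned test is faulty or that the primary objective is underpowered because of it.

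**What to change.** In the primary-outcome analysis under {20a}, specify the step-down Dunnett test: compare the larger |t| with the Dunnett critical value and, if it is significant, test the other dose at two-sided 5%. Report step-down adjusted p-values and state whether the 95% CIs are simultaneous. If they are, add a footnote that a second dose with |t| between about 1.985 and 2.245 will be significant while its interval includes 0. Since the continuous secondary outcomes use the same method, say whether the change applies to them.

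The change needs no patients and uses a standard procedure. It is more than an edit, though: recruitment began in December 2019, and the article requires IRB approval and a signed agreement for each protocol revision. It should be made by protocol or SAP amendment before unblinding. The other cost is the higher chance, still below 5%, of declaring an inert dose when the other works.
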